# Specific committee for the study

## Steering Committee

**Members of the committee**: [name] (Primary investigator, anaesthesiologist), [name] (scientific coordinator, emergency physician), [name] (emergency physician), [name] (Cardiologist), [name] (geriatrician), [name] (clinical pharmacologist; and Methodologist), [name] (statistician), a representant of the promotor (DRCI head office project advisor)

**Missions:**Define the overall structure of the study, coordinate information, review the initial methodology and oversee the trial.

The committee can be asked to adjudicate any death in the study and relate whether it is from cardiovascular cause.

Rhythm of the meeting: 1meeting per years.

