# SCIENTIFIC JUSTIFICATION FOR THE RESEARCH

## CURRENT KNOWLEDGE

Acute heart failure (AHF) is a syndrome defined as new-onset or worsening of symptoms and signs of HF,often requiring rapid escalation of therapy and hospital admission. The clinical presentation of AHF typically includes symptoms or signs related to congestion and volume overload rather than to hypoperfusion.^1^ Acute heart failure represents 5% of all emergency hospitalizations, and is the most common primary diagnosis in patients ≥75 years visiting the ED.^2,3^ The ED are the main entry to the hospital for AHF, with 64% of these admissions being subsequent to an ED visit.^4^ This syndrome is reportedly associated with poor outcomes, with a 80% rate of hospital admission, a median length of hospital stay of 10 days and a mortality around 10% at 30 days, and a readmission rate of 25-30% at 30 days.^5–7^

Despite a high rate of morbidity and mortality, the management of AHF has not changed for several decades and most clinical studies failed to demonstrate a positive impact of new drugs on patients’ prognosis.^8,9^European guidelines include the use of diuretics, nitrates, oxygen and non-invasive ventilation (NIV) when indicated along with the treatment of any potential AHF triggers (precipitating factors).However, these guidelines are based on moderate levels of evidence (IB and IIaB), and high-quality randomized controlled trials data (RCT) are lacking.^10–12^

In 1998 and 2000, the two cornerstones trials of Cotter et al. provided evidences of benefits associated with early vasodilatator therapy with nitrates, although on a very small sample of patients (less than 200 in total).^13,14^ Since then, every prospective trial on AHF management failed to report a clinical significant improvement of outcomes. Equipoise remains on many questions regarding the recommended therapeutics: the optimum dose and route of administration of diuretics are not clear, the use of nitrates is also debated, and the benefit of non-invasive ventilation (NIV) is unclear.^15–17^

Despite these controversies, recommendations and guidelines are published by international society (ESC, AHA, …) and constitute the basis of our understanding and standard of care.^10,11^ However, a large proportion of elderly patients in AHF do not receive adequate care, including low rate (30-50%) of nitrates therapy.^7,18,19^

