## Secondary endpoints

- 30 day all-cause mortality
- 30 day cardio-vascular mortality
- Hospital readmission at 30 days
- Length of in hospital stay truncated at 30 days
- Changes of more than 2 fold in creatinine level from inclusionto day 30 or to discharge whichever comes first.

Creatinine will be measured at day 0 in the ED, and at discharge day or day30, whichever comes first.

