| Center 11 | C | C | C | C | C | C | C | … | I | I | I | I | I |
| Center 12 | C | C | C | C | C | C | C | … | I+T | I | I | I | I |
| Center 13 | C | C | C | C | C | C | C | … | C | I+T | I | I | I |
| Center 14 | C | C | C | C | C | C | C | … | C | C | I+T | I | I |
| Center 15 | C | C | C | C | C | C | C | … | C | C | C | I+T | I |

*Figure 1: stepped wedge organisation and timetable of the trial*

C: Control period. I: Intervention period. T: training

**In the case where one or more centers will have to drop out of the trial, a mid-term reevaluation of the period distribution will be conducted by the steering committee in order to ensure similar repartitions of period and number of patients in each group.**

This trial is comparative: intervention period vs control period. In the intervention period, patients will be treated according to the care bundle. In the control period, patients will be treated as usual (TAU) by the emergency physicians, without the aid of a care bundle.

Due to the design of the study (stepped wedge) and the intervention, there will be no blinding of the physician and the patient.

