### Randomization

This is a stepped wedge randomisation. All centers will be randomised for their time of intervention implementation. Randomisation will be computer generated by a biostatistician from URC-Est, independent of the study and before the study beginning.

This is an open trial.

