## Anticipated methods and timetable for measuring, collecting and analyzing the efficacy data

- In-hospital mortality will be obtained from hospital data base (Mediweb, Gilda, or Orbis) and phone interview with the last known ward of hospitalization of the patient. In case of transfer to another hospital, this data will be collected either by phone interview or hospital visit if necessary.
- 30 day all-causes mortality rate: same as above for patient still in hospital at day 30, phone call to the patients, relatives, or GP if not.
- Cardiovascular related 30 day mortality. Adjudicated by an adjudication committee (see below) as to whether the death has been mainly caused by a cardiovascular issue.
- Length of stay in hospital and changes of more than 2 fold in creatinine level from hospital database (CleanWeb, MediWeb, Gilda or Orbis)
- Efficacy data will be analyzed at the end of the study after data review and freezing of data base.

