### Strategy for site opening

The strategy for opening the centers will be determined before the research begins.

Opening visit will be carried out by the local investigator and at least one member of the steering committee and one member of URC-Est. ED physicians will be invited to participate in the opening session in each center. A similar visit will occur at the time of the period switch, with the presence of one member of URC-Est, one member of the steering committee and the local investigator.

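### Committee adjudication is the stated method for 30-day cardiovascular death, but the only committee described may merely be asked to do it, and no masking is stated

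*Protocol*

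**What the plan says.** Protocol section 4.2 lists "30 day cardio-vascular mortality" as a secondary endpoint. Section 9.2 gives its method without condition: "Adjudicated by an adjudication committee (see below) as to whether the death has been mainly caused by a cardiovascular issue".

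The only committee described after that point is the steering committee in 11.1. Its members include the primary investigator, the scientific coordinator, a further emergency physician, a cardiologist, a geriatrician, a methodologist and a statistician. On causes of death the section says: "The committee can be asked to adjudicate any death in the study and relate whether it is from cardiovascular cause". It also says: "Rhythm of the meeting: 1meeting per years".

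On masking, section 5.1 says "there will be no blinding of the physician and the patient", and the Randomization part of 5.3 says "This is an open trial". Under Strategy for site opening (14.1), the visit at each centre's switch takes place "with the presence of one member of URC-Est, one member of the steering committee and the local investigator". Nothing is said about whether those who classify deaths see the centre, the date or the period.

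**The concern.** The two sections give different rules for one endpoint. In 9.2 adjudication is how the endpoint is measured; in 11.1 it is something the committee may be asked to do. The protocol does not say who asks, for which deaths, or who classifies a death that is not referred. If referral is left to choice in an open trial, the choice can differ between periods.

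Cause of death is also a matter of judgement here. Patients are 75 or older, and the triggers named in the background are infection, acute coronary syndrome and atrial fibrillation. The only criterion is that the death was mainly cardiovascular. The bundle itself makes physicians look for and record those triggers, whereas 23 of 73 patients (32%) in the preliminary survey (section 2.1) had not been investigated for them. The files may therefore differ by period in ways that steer a reader towards one cause. In a stepped wedge, centre plus date reveals the period, so an unredacted file discloses the allocation. A later analysis cannot undo classification bias of this kind.

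**Working it through.** **Inputs**
- 500 patients included (13.4).
- 30-day mortality: "a mortality around 10% at 30 days" (2.1).
- Allocation: in Figure 1 the centres spend 2, 3, …, 16 two-week periods under control. These sum to 135 of 15 × 18 = 270 centre-periods, so the split is 1:1. With even recruitment that is 250 v 250.
- Cardiovascular share of deaths: not in the protocol. Assumed 50–80%.
- Test level 5% (13.5), taken as two-sided. Section 13.3 names Pearson's chi-square or Fisher's exact test for this endpoint.

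**The plan's own figures.** The protocol gives none for cardiovascular death. Its overall size reproduces closely: 283 × 1.609 = 455 (stated 454), and 454 × 1.10 = 499 (stated 500).

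**Expected events.** 500 × 0.10 = 50 deaths, 25 per period. Cardiovascular: 50 × 0.50 = 25 to 50 × 0.80 = 40. At a 60% share, 25 × 0.60 = 15 per period.

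**Effect on the estimate.** Start with no true difference and move deaths out of the cardiovascular class in the intervention period only.

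| Share | Per period | 2 moved | 3 moved |
|---|---|---|---|
| 50% | 12.5 | 10.5/12.5 = 0.84 | 9.5/12.5 = 0.76 |
| 60% | 15 | 13/15 = 0.87 | 12/15 = 0.80 |
| 80% | 20 | 18/20 = 0.90 | 17/20 = 0.85 |

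For 12 v 15 the standard error of log RR is √(1/12 + 1/15 − 2/250) = 0.377. The 95% CI is 0.80 × exp(±1.96 × 0.377) = 0.38 to 1.67. The chi-square p is about 0.55.

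**Effect on significance.** Uncorrected chi-square, 250 v 250, written as control v intervention: z = (difference in proportions)/√(2p̄(1 − p̄)/250). Example for 21 v 10: p̄ = 31/500 = 0.062, difference = 11/250 = 0.044, z = 0.044/0.0216 = 2.04, p = 0.041.

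| Start | p | Deaths reclassified | End | p |
|---|---|---|---|---|
| 21 v 10 | 0.041 | 1 | 21 v 11 | 0.068 |
| 21 v 9 | 0.024 | 2 | 21 v 11 | 0.068 |
| 20 v 10 | 0.060 | 1 | 20 v 9 | 0.035 |
| 18 v 12 | 0.26 | 4 | 18 v 8 | 0.044 |
| 15 v 15 | 1.00 | 9 | 15 v 6 | 0.045 |

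Across the 50–80% range, starting from balance (or one death away from it), 8 to 12 reclassifications are needed, depending on the share and on whether they fall in one period or both. That is 16–24% of all deaths.

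These tests ignore clustering and time. Fisher's test gives larger p-values (20 v 9: 0.054).

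**The case against.** **A body does exist.** A reader might infer that the promised committee is never set up. The text does not support that. The pointer in 9.2 most naturally leads to the steering committee, which has listed members, a cardiologist and a geriatrician among them, and is given this very task. The gap lies in the name and the duty.

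**Optional referral is a reading.** The sentence in 11.1 could be taken as giving the committee authority over any death, with 9.2 supplying the obligation. That is possible, but the wording of 11.1 is permissive and no other sentence requires every death to be sent. The protocol does not say that deaths will be selected differently by period; it only leaves room for it.

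**Unmasked is an inference.** The no-blinding statement names physicians and patients, not adjudicators, and masking could be set out in a charter that is not shown. The inference is still reasonable: the trial is open, a committee member attends each switch, and the protocol settles who adjudicates without any masking condition.

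**The numbers are modest.** It is tempting to say that a few borderline deaths could create or hide an effect. The calculation does not support that as a general claim: three moved deaths give p of about 0.55. A cardiovascular difference produced by reclassification would also stand beside an unchanged all-cause result, where readers could see the discrepancy.

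**Redaction has limits.** Antiplatelets, antibiotics and ventilation bear on the cause of death and may continue on the ward, so the file can still hint at the period. This stands.

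**Conclusion.** The point holds in a limited form. Sections 9.2 and 11.1 disagree on whether adjudication is the rule or an option, and no masking is stated for a committee that oversees an open trial.

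The plausible distortion is a shift in the estimate: a risk ratio of about 0.87 to 0.80 for two or three misclassified deaths at 15 v 15 (0.90 to 0.76 over the assumed 50–80% share), with no true effect and no statistical significance. Significance turns on one or two deaths only when the result is already near 0.05.

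This rests on 10% mortality, equal recruitment by period, the assumed cardiovascular share, and tests that ignore clustering. Only this secondary endpoint is affected. The primary endpoint scores any death as 0, and all-cause mortality needs no cause. It is a worthwhile, inexpensive improvement and does not threaten the trial's main conclusion.

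**What to change.** In 11.1, replace the permissive sentence with a duty along these lines: the clinician members adjudicate every death up to day 30, against a written definition of cardiovascular death, from dossiers with centre, dates, period and the bundle checklist removed; no member judges a death from their own centre. In 9.2, name this committee in place of the unnamed one. The yearly meeting rhythm should allow for this work; the study lasts 36 weeks and 30 days, so one adjudication session after the last follow-up could cover all deaths.

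Cost: clerical time for existing research staff to redact about 50 dossiers. Sample size, visits and patient care do not change. Masking will be incomplete, because treatments relevant to the cause of death may have to stay in the file and can hint at the period. Judges from outside the trial team would be stronger still, but the change above removes the contradiction and reduces the bias with the committee already in place.

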# data management

## Data collection

Data will be collected in an electronic case report form (e-CRF), devised by the study coordinator in collaboration with URC-EST. Baseline data will be completed by the investigators with the help of a Clinical Research Technician (CRT) of URC-Est for AP-HP centers and a local Clinical Research Technician for other centers.

## Identification of data recorded directly in the CRF which will be considered as source data

After inclusion, the local investigator, emergency physician, with the help of the CRT if present, will complete ae-CRF that contains inclusion/exclusion criteria, main baseline characteristics and will complete the handover checklist (care bundle Figure 2).
The outstanding variables will be collected through the review of electronic medical chart of ED visit (Urqual in most centers).

Data regarding follow up, survival and hospital evolution will be collected through the review of electronic medical chart of ward hospitalization (MEdiweb), administrative software (Gilda / Orbis) or if needed physicians’/CRT phone call.

## Right to access source data and documents

### Data access

In accordance with GCP:

- the sponsor is responsible for ensuring all parties involved in the study agree to guarantee direct access to all locations where the study will be carried out, the source data, the source documents and the reports, for the purposes of the sponsor's quality control and audit procedures.

- the investigators will ensure the persons in charge of monitoring and auditing the research and of quality control have access to the documents and personal data strictly necessary for these tasks, in accordance with the statutory and regulatory provisions in force.

### Source documents

The source documents are any original document or item that proves the existence or accuracy of a data-point or fact recorded during the study. Source documents will be kept by the investigator, or by the hospital in the case of hospital medical records, for the statutory period.

That will include:

- handover checklist and treatment list
- Medical chart, laboratory test results and imaging reports from the initial (or repeated) hospitalisation

### Data protection

The persons responsible for the quality control of clinical studies (Article L.1121-3 of the Code de la Santé Publique - CSP (French Public Health Code) will take all necessary precautions to ensure the confidentiality of information relating to the research, the participants and in particular their identity and the results obtained.

These persons, as well as the investigators themselves, are bound by professional secrecy (in accordance with the conditions set out in Articles 226-13 and 226-14 of the French Criminal Code).

During and after the research, all data collected about the participants and sent to the sponsor by the investigators (or any other specialized collaborators) will be anonymized.

Under no circumstances will the names and addresses of the participants be shown.

The sponsor will ensure that each participant has agreed in writing for any personal information about him or her which is strictly necessary for the quality control of the study to be accessed.

## Data processing and storage of research documents and data

### Identification of the person responsible and the location for data processing

Data management will be performed by a data manager from URC-Est under the responsibility of [name]. Statistical analysis will be performed by a biostatistician from URC-Est under the responsibility of [name] ([name]).

### Data entry

Data will be entered electronically via a web browser.

### Data processing (CNIL, the French Data Protection Authority)

This research is governed by the CNIL "Reference Method for processing personal data for clinical studies" (MR-001, amended). AP-HP, the sponsor, has signed a declaration of compliance with this "Reference Method" Adapt based on the internal procedures of the data management entity

All personal data for this research will be processed in accordance with Chapter IX of the amended French Data Protection Act of 6 January 1978 (articles 53-61).

### Archiving

All specific documents for Minimal Risk and Restriction research studies are to be archived by the investigator and the sponsor for 15 years after the end of the research.

This indexed archiving applies to:

- A sealed envelope for the investigator, containing one original of all information sheets and consent forms signed by all individuals at the site who participated in the research;
- A sealed envelope for the sponsor, containing one copy of all information sheets and consent forms signed by all individuals at the site who participated in the research;
- "Study" binders for the Investigator and the sponsor, containing (non-exhaustive list):
- all successive versions of the protocol (identified by version no. and date), and its appendices
- decisions of the CPP
- correspondence
- the enrolment list or register
- the appendices specific to the research
- Final report
- The case report forms

## Ownership of the data

AP-HP is the owner of the data. The data cannot be used or disclosed to a third party without its prior permission.

# statistical aspects

## Description of statistical methods to be used including the timetable for the planned interim analyses

No interim analysis is planned. Analysis will be performed at the end of the study after data review and freezing of data base.

Analyses will be performed using SAS® software (version 9.3 or updated version).

Principal analysis will be realized according to the ITT principle.

Baseline patient’s characteristics will be considered at both with the cluster (center) and patient level.

For the center level, characteristics at the beginning of the study will be described (there are no expected change between the two periods for cluster characteristics).

Baseline characteristics of patients will be described globally and according to the period. Continuous variables will be summarized using descriptive statistics, i.e number of subjects, mean, standard deviation (s.d), median, inter quartile range, minimum and maximum. Qualitative variables will be summarized by frequency and percentage.

Number of cross-over from one group to the other group will be described.

## Principal criterion analysis

The number of days alive and out of hospital will be calculated based on date of admission, vital status, date of death and date of discharge will be collected. A death during follow-up will correspond to 0. An ED visit will correspond to “one day” at the hospital.

The number of days alive and out of hospital will be analysed using a linear regression mixed model with a random effect for each cluster, considered fixed effects will be: strategy and, for the stepped wedge design, time representing each step. In case of non-normality distribution of the interest variable, a transformation could be realized.

## Secondary evaluation criteria

In hospital mortality, all causes mortality at 30 days and cardiovascular mortality at 30 days will be compared between groups by using Pearson's chi-square test or Fisher exact test.

If possible, generalized linear regression mixed model with Poisson distribution will be performed. If the number of events is sufficient, generalized linear regression mixed model using logit link will be performed.

The length of stay in hospital in days will be compared between the two periods by using Student t-test or Wilcoxon rank-sum test as needed. If possible, a linear regression mixed model will be performed. A random effect for each cluster will be considered and considered fixed effects will be: strategy and, for the stepped wedge design, time representing each step. In case of non-normality distribution of the interest variable, a transformation could be realized.

Percentage of patients with a change of more than 2 fold in creatinine between inclusion and 30 days will be compared between groups by using Pearson's chi-square test or Fisher exact test. If possible, generalized linear regression mixed model with Poisson distribution will be performed. If the number of events is sufficient, generalized linear regression mixed model using logit link will be performed.

Second analysis will be performed on the per protocol population.

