| Statistical analysis | No interim analysis is planned. Analysis will be performed at the end of the study after data review and freezing of data base according to ITT principle and with regard to cluster level randomisation. |
| Sources of monetary support | French ministry of health |

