# Research methodology

## Design of the study

The ELISABETH trial is designed as a stepped wedge cluster randomized trial. We decided to choose this design for the following reasons:

- As we implement a new protocol, there is a risk of contamination. An emergency physician, who would have already treated patients via the care bundle protocol, would be subsequently influenced by this trial, and could have difficulty to provide the former “standard of care”. Therefore, a randomization at the patient level or a cross-over design would induce bias through contamination. This bias was likely a reason why the recent “Guide It” trial failed to provide significant difference between control group and intervention group.^39^
- The present ELISABETH trial focus on a severe condition, in EDs that are often busy places, therefore the need for a randomization at the patient level could be an impediment to inclusion, and therefore limit our ability to recruit consecutive patients
- A cluster stepped-wedge design prevents contamination as centers will first be allocated to standard care, before implementing the intervention. Furthermore, a stepped wedge design would also prevent a potential “period effect” that could have resulted from a simple cluster before/after design

All the 15 participating centers will begin with a “control period” for 4 weeks. Then, every 2 weeks, one center will be randomized to switch to the “intervention period”. After 32 weeks, all centers will then be in the intervention group for a last 4-week period.

| **Weeks** | **1-2** | **3-4** | **5-6** | **7-8** | **9-10** | **11-12** | **13-14** | **…** | **27-28** | **29-30** | **31-32** | **33-34** | **35-36** |
| --- | --- | --- | --- | --- | --- | --- | --- | --- | --- | --- | --- | --- | --- |
| Center 1 | C | C | I+T | I | I | I | I | … | I | I | I | I | I |
| Center 2 | C | C | C | I+T | I | I | I | … | I | I | I | I | I |
| Center 3 | C | C | C | C | I+T | I | I | … | I | I | I | I | I |
| Center 4 | C | C | C | C | C | I+T | I | … | I | I | I | I | I |
| Center 5 | C | C | C | C | C | C | I+T | … | I | I | I | I | I |
| Center 6 | C | C | C | C | C | C | C | … | I | I | I | I | I |
| Center 7 | C | C | C | C | C | C | C | … | I | I | I | I | I |
| Center 8 | C | C | C | C | C | C | C | … | I | I | I | I | I |
| Center 9 | C | C | C | C | C | C | C | … | I | I | I | I | I |
| Center 10 | C | C | C | C | C | C | C | … | I | I | I | I | I |

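### Unadjusted two-group tests are the default for mortality, length of stay and creatinine, and the time- and centre-adjusted model is optional, so part of any calendar trend can pass for a treatment effect

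*Protocol*

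**What the plan says.** Section 13.3 takes the secondary endpoints in turn.

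- **Mortality** (in hospital, all-cause and cardiovascular): "cardiovascular mortality at 30 days will be compared between groups by using Pearson's chi-square test or Fisher exact test". Then: "If possible, generalized linear regression mixed model with Poisson distribution will be performed". A logit version is added if there are enough events. Neither model has its random or fixed effects listed.
- **Length of stay**: "The length of stay in hospital in days will be compared between the two periods by using Student t-test or Wilcoxon rank-sum test as needed". Then: "If possible, a linear regression mixed model will be performed". Here a random centre effect is named, and "considered fixed effects will be: strategy and, for the stepped wedge design, time representing each step".
- **Creatinine more than doubled**: the same crude tests and the same conditional models as for mortality, again with no effects listed.

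Three other places bear on this. Section 13.2 gives the primary endpoint a linear mixed model with random centre, strategy and time, without condition. The Summary promises analysis "according to ITT principle and with regard to cluster level randomisation". Section 5.1 argues that "a stepped wedge design would also prevent a potential" period effect of the kind that a plain before/after cluster design would suffer.

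**The concern.** In a stepped wedge every centre moves from control to intervention and none moves back, so intervention patients come systematically later than control patients. The design protects against a period effect only if the analysis contains time. A chi-square, Fisher, t or Wilcoxon test of intervention against control patients contains neither time nor centre. It therefore compares later patients with earlier ones, and a seasonal or secular change in mortality or length of stay moves the result in whichever direction the trend runs.

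The mortality outcomes are the most exposed. Section 2.1 puts 30-day mortality at about 10%, which is about 50 deaths in 500 patients (0.10 × 500). Spread over the baseline and 15 switches (16 time levels), that is about 3 deaths per level (50/16 = 3.1), and cardiovascular deaths will be fewer. The condition on the mixed model may well fail there, and the crude p-value would then be the only inference on death. If both analyses run, section 13.5 tests each at 5%, and the protocol does not say which one counts.

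**Working it through.** Section 13.3 gives no figure to reproduce, so the check uses the schedule.

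**Inputs from the protocol.** Figure 1: 15 centres and 18 fortnights, centre *k* switching in fortnight *k* + 2. Section 13.4: 454 patients analysed, 500 included, ICC 0.0001. Section 13.5: 5% level (two-sided assumed). Section 2.1: 30-day mortality about 10%.

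**Assumptions.** Equal expected recruitment per centre-fortnight; a linear trend; no treatment effect; SD of length of stay 8 or 9 days (9 is borrowed from the primary endpoint in section 13.4); an ICC of 0.05 as a sensitivity value.

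**Step 1: imbalance in calendar time.** Centre *k* contributes *k* + 1 control fortnights. The sum over *k* = 1 to 15 is 120 + 15 = 135 control cells, which leaves 270 − 135 = 135 intervention cells. Fortnight *p* has its midpoint at week 2*p* − 1, so centre *k*'s control midpoints sum to (*k* + 1)². Over all centres this is 2² + … + 16² = 1495.

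- Mean control midpoint: 1495/135 = 11.07 weeks.
- Mean intervention midpoint: 36 − 11.07 = 24.93 weeks.
- Gap: 13.85 weeks.

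**Step 2: share of a linear trend that enters the crude contrast.** 13.85/36 = 38% of a change over the full 36 weeks. If the drift is measured from first to last fortnight midpoint (34 weeks), the same gap is 13.85/34 = 41%. Only the denominator differs. On the second scale, mortality drifting from 12% to 8% shows as 10.8% against 9.2%, and from 14% to 6% as 11.6% against 8.4%, with no treatment effect.

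**Step 3: type I error by formula, N = 500.** Rejection = Φ(|b|/SE − 1.96) + Φ(−|b|/SE − 1.96), with *b* the bias.

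- Mortality 14% to 8%: *b* = 6 × 0.385 = 2.3 points; SE = √(4 × 0.11 × 0.89/500) = 2.8 points; ratio 0.82; rejection 13%.
- Length of stay, 2-day drift, SD 8: *b* = 0.77 day; SE = 8 × √(4/500) = 0.72 day; ratio 1.08; rejection 19%.

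**Step 4: type I error by simulation on the Figure 1 schedule** (drift from first to last fortnight; 4,000 runs per crude mortality setting, 1,500 per other setting).

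| Crude chi-square, mortality | N = 454 | N = 500 |
|---|---|---|
| Flat 10% | 4.5% | 5.0% |
| 12% to 8% | 8.1% | 9.1% |
| 14% to 6% | 21.9% | 24.0% |

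| Crude t-test, length of stay, SD 9, N = 454 | ICC 0.0001 | ICC 0.05 |
|---|---|---|
| No drift | 5.1% | 7.7% |
| 1 day | 8.2% | 13.2% |
| 2 days | 15.7% | 19.6% |
| 3 days | 29.1% | 32.2% |

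**Step 5: the same data with adjustment.** With period in the model, mortality rejects at 4.9%, 5.2% and 5.0% for the three settings (N = 454). With centre and period in the model, length of stay rejects at 4.1% to 5.9% throughout. Centre was fitted as a fixed effect in this check; the protocol's model has it random.

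**The case against.** The adjusted models are already planned. Section 13.3 attaches a mixed model to each endpoint it analyses, and for length of stay the specification matches that of the primary analysis. The protocol never says that the crude test is the one to interpret, and a SAP that is not at hand could rank the two. With about 50 deaths, some caution about convergence is reasonable. The primary endpoint already combines death and hospital days and is analysed properly. All of this is fair. What stands is that the protocol itself fixes the unsuitable test without condition and the suitable model with one, and names no fallback that keeps time.

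A reader might infer more than the documents support:

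- *That a whole secular trend becomes a treatment effect.* Only about 38% of a linear 36-week change does. A seasonal pattern that is not monotone could leak more or almost nothing.
- *That the secondary p-values are bound to be wrong.* With no trend and the protocol's ICC, the crude tests hold about 5%. A fall from 14% to 6% in 36 weeks is a strong assumption.
- *That clustering is the main fault.* At ICC 0.0001 it adds nearly nothing. The 7.7% with no drift needs an ICC of 0.05, which is 500 times the protocol's value.
- *That section 13.3 flatly contradicts the Summary.* It undercuts the promise to respect cluster randomisation by making the cluster model optional, but the model is there.
- *That the Poisson model for binary outcomes makes matters worse.* Without a robust variance its standard errors are slightly too wide, which errs on the cautious side and is no part of this point.

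**Conclusion.** The point holds for mortality, length of stay and creatinine. The default tests are confounded with calendar time by the design itself, and the protection that section 5.1 claims is lost wherever the optional model is not fitted or not preferred. The 38% share follows from Figure 1 and even recruitment. The error rates depend on assumed trends: near 5% with none, about 8-9% for mortality from 12% to 8%, 13% for 14% to 8%, and 22-24% for 14% to 6%. For length of stay they are about 8% for a 1-day drift and 16-19% for a 2-day drift, at an assumed SD of 8 to 9 days. The bias can favour or penalise the bundle. The primary analysis in section 13.2 is not touched. Readmission is outside this point, because section 13.3 names no test for it.

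**What to change.** In section 13.3, state that for mortality, length of stay and creatinine the inferential analysis is the mixed model with random centre, fixed strategy and fixed time, as in section 13.2. Write those effects out for the binary endpoints too. Keep the crude proportions, means and comparisons as description only.

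Name in advance a fallback for sparse events that still adjusts for time and centre, such as coarser time blocks or a smooth time term, and exclude a return to a test without time. If a robust variance is used, add a small-sample correction, since there are only 15 clusters.

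The change should be made before the data are seen, so that nobody chooses between crude and adjusted results afterwards. It costs wording only, because the models are already foreseen. The price is wider confidence intervals than the crude tests would show.
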